## Visit Checklist

Village: (1) Guilin; (2) Jianzheng; (3) Qianfeng; (4) Yixue; (5) Xinsheng; (6) Yijia; (7) Huanglian; (8) Tiane

Participant's name: \_\_\_\_\_ Sex: Male ☐ Female ☐

Tel:

ID number:

| No. | SAWA Assessments                                   | Notes                                                    | Investigator's Signature |
|-----|----------------------------------------------------|----------------------------------------------------------|--------------------------|
| 1   | Weight                                             | kg                                                       |                          |
| 2   | Percentage Body Fat                                | %                                                        |                          |
| 3   | Visceral Fat                                       |                                                          |                          |
| 4   | Height                                             | cm                                                       |                          |
| 5   | Waist Circumference                                | cm                                                       |                          |
| 6   | Hip Circumference                                  | cm                                                       |                          |
| 7   | Blood Pressure
(Systolic/Diastolic
Pressure) | mmHg                                                     |                          |
|     |                                                    | mmHg                                                     |                          |
|     |                                                    | mmHg                                                     |                          |
| 8   | Questionnaires                                     | Yes  No  |                          |

Quality Control Staff' Signature \_\_\_\_\_

Date \_\_\_\_\_

---

## **Appendix B: Intervention Materials**

- **Telephone Counseling Techniques**
- **Telephone Counseling Record**

---

## **Telephone Counseling Techniques**

### **(1) Telephone Counseling Template for the First Time**

#### **a. Telephone counseling process (group leader)**

1. First of all, please ask: Hello, is this xxx?
2. Descript the intention of this call: We are the investigators performed physical activity (PA) training and questionnaire survey for you several days ago. Now we need to ask you some questions, can you please make it convenient for us now? (if it's not convenient now, ask the nearest available time)
3. Primary contents
  - 1) Recent exercise situation: What types of exercise were you performing recently, how many times a day, and how many minutes each time for performing PA?
  - 2) Set exercise goals: Your current exercise intensity is (great/okay/not enough), next week you can perform (moderate-intensity PA such as Tai Chi: 2 times a day and 20 minutes for each time or 40 minutes a day; vigorous-intensity PA such as running: 2 times a day and 15 minutes for each time or 20 minutes a day). We will call you every week to see if you have reached your goals.
  - 3) Peer group: We assisted you form a peer group to exercise together after the PA training, do you remember that? You are the leader of group x (e.g., 1) and the group has xx members, including xx, xx, and xx. What kind of exercise do you think is better for your group to perform together? How many times a week can you get together to exercise, and how many minutes for each time? Okay, then your group exercise goal is to xx (e.g., dance five times a week and 40 minutes for each time). Do you think it is okay? Please don't forget to organize your members to exercise together.

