## Overview of Trial Design

### Design

This study is a single-blinded cluster randomized controlled trial to test the effect and sustainability of the multilevel PA intervention to improve PA levels in rural older adults. There were 8 villages participating in total: 4 intervention sites and 4 control sites. RE-AIM (Research, Efficacy, Adoption, Implementation, and Maintenance) will be applied to evaluate the pre-post and intervention-control differences as well as external validity.

[figure not shown]

---

Figure 1. Overview of SAWA Intervention

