## Interventions

In light of current evidence on PA intervention and follow-up periods, our project will consist of an 8-week intervention and a 24-month follow-up. The intervention group will receive the intervention from May to July 2021. Figure 2 shows the timeline of the 8-week intervention strategies.

| Level               | Intervention strategies | 1 wk | 2 wk | 3 wk | 4 wk | 5 wk | 6 wk | 7 wk | 8 wk |
|---------------------|-------------------------|------|------|------|------|------|------|------|------|
| Individual level    | Telephone counseling    | x    | x    | x    | x    | x    | x    | x    | x    |
|                     | Printed materials       | x    | x    | x    | x    | x    | x    | x    | x    |
|                     | Training sessions       | x    |      |      | x    |      |      |      | x    |
| Interpersonal level | Peer group              | x    | x    | x    | x    | x    | x    | x    | x    |
| Community level     | Group sharing           | x    |      |      | x    |      |      |      | x    |
|                     | Coaching                | x    |      |      | x    |      |      |      | x    |

Figure 2. Timeline of the 8-week Intervention Strategies

The underlying theoretical model used to motivate the participants is derived from the socio-ecological model (SEM). The SEM consists of five dimensions: individual, interpersonal, community, organizational, and public policy levels, which are thought to be the determinants of health-related behavior. It emphasize the dynamic interaction among biological, psychological, behavioral, social, and environmental factors. Systematic reviews from intervention studies based on the SEM have revealed the effectiveness of such interventions, indicating that not only PA level was increased, but sedentary time was reduced. For the current study, a condensed version of the SEM consisting of 3 levels of influence were utilized: individual, interpersonal, and community levels. Our detailed interventions based on the three levels (individual, interpersonal, and community levels) are as follows:

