### Telephone Counseling

The participants will receive the feedback on their PA and health behaviors in relation to the recommendations through the telephone counseling. This feedback will also highlight the discrepancy between their health and PA goals. The telephone call will be used to encourage participants to exercise and provide individualized assistance as follows: 1) set the exercise goals based on their preference and the intensity of their daily exercise, 2) participants will be asked “did you achieve the exercise goals last week?”, 3) investigators will praise the respondents who have achieved the goals, and adjust them according to the global recommendations on PA for older adults, 4) participants who did not achieve the goals will be encouraged, and investigators will assist them to solve the difficulties.

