### Training Sessions

The training sessions will be taught by sports experts who are certified to engage in physical education. Stretching exercises and Tai Chi will be mainly included in the

---

courses. Stretching exercise was a complement to other exercises. Tai Chi is a moderate-intensity exercise that has been supported in the literature for improving cognitive function and preventing clinical diseases, such as Parkinson's disease, osteoarthritis, and so on

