### Quantitative surveys

*The following data will be collected based on the questionnaires by trained investigators.*

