### **Outcomes**

Our primary outcome is the changes in leisure-time activity at 8 weeks. Our secondary outcomes include household activity, work-related activity, total PA, proportions of meeting WHO recommendations, leisure-time preferences, sedentary behavior, self-efficacy, self-regulation, self-rated health, cognitive function, night-time sleep quality, weight, percentage weight change, body mass index, percentage body fat, visceral fat, waist circumference, hip circumference, waist-to-hip ratio, waist-to-height ratio, and systolic and diastolic blood pressure at all assessment time, as well as the leisure-time activity at 4 weeks, 6 months, 12 months, and 24 months.

---

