## Physical Activity Scale for the Elderly

### 1. Leisure-time Physical Activity

1.1 Have you walked outside home in the past week? For example, walking the dog, exercising, and walking to and from work.

(1) never (skip to question 1.1.c); (2) seldom (1-2 days); (3) sometimes (3-4 days); (4) often (5-7 days)

1.1.a How much time do you usually spend doing these things each day?

(1) < 1 hour; (2) 1-2 hours; (3) 2-4 hours; (4) > 4 hours

1.1.b How many kilometers do you usually walk per day?

(1) < 0.5 km; (2) 0.5-1 km; (3) 1-2 km; (4) > 2 km

1.2 In the past week, how did you participate in light sports such as fishing?

(1) never (skip to question 1.2.c); (2) seldom (1-2 days); (3) sometimes (3-4 days); (4) often (5-7 days)

1.2.a What are the specific activities: \_\_\_\_\_

1.2.b How much time do you usually spend doing these things each day?

(1) < 1 hour; (2) 1-2 hours; (3) 2-4 hours; (4) > 4 hours

1.3 In the past week, how did you participate in moderate sports such as table tennis, dancing, or tai chi?

(1) never (skip to question 1.3.c); (2) seldom (1-2 days); (3) sometimes (3-4 days); (4) often (5-7 days)

1.3.a What are the specific activities: \_\_\_\_\_

1.3.b How much time do you usually spend doing these things each day?

(1) < 1 hour; (2) 1-2 hours; (3) 2-4 hours; (4) > 4 hours

---

1.4 In the past week, how did you participate in strenuous sports such as jogging, cycling, or swimming?

(1) never (skip to question 1.4.c); (2) seldom (1-2 days); (3) sometimes (3-4 days); (4) often (5-7 days)

1.4.a What are the specific activities: \_\_\_\_\_

1.4.b How much time do you usually spend doing these things each day?

(1) < 1 hour; (2) 1-2 hours; (3) 2-4 hours; (4) > 4 hours

1.5 In the past week, how did you participate in muscle strength / endurance exercises such as weight lifting, bench press, or push-ups?

(1) never (skip to question 1.5.c); (2) seldom (1-2 days); (3) sometimes (3-4 days); (4) often (5-7 days)

1.5.a What are the specific activities: \_\_\_\_\_

1.5.b How much time do you usually spend doing these things each day?

(1) < 1 hour; (2) 1-2 hours; (3) 2-4 hours; (4) > 4 hours

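### Who is blinded is undefined, the call scripts blur trainers with interviewers, and study-run Tai Chi can fall in the 8-week recall week, so the self-reported primary outcome is at risk of bias towards the intervention

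*Supplement*

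**What the plan says.** All references are to the final protocol.

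- **Outcome.** Under Outcomes: "Our primary outcome is the changes in leisure-time activity at 8 weeks". The outcome list contains no device-based activity measure. Quantitative surveys introduces the questionnaire data thus: "The following data will be collected based on the questionnaires by trained investigators".
- **Blinding.** Design states: "This study is a single-blinded cluster randomized controlled trial". No section says which party is blind.
- **Call scripts (Appendix B, Telephone Counseling Techniques).** The first-call script for group leaders opens with "We are the investigators performed physical activity (PA) training and questionnaire survey for you several days ago". The first-call script for all participants and both weekly scripts use nearly the same greeting. Under Telephone Counseling, "investigators will praise the respondents who have achieved the goals".
- **Separate teams.** Data Management and monitoring and Assessment Team give outcome collection at every visit to an assessment team. Training Sessions gives the teaching to certified sports experts. Intervention and education teams are also named.
- **Session timing and content.** The table headed "Figure 2. Timeline of the 8-week Intervention Strategies" marks training sessions in weeks 1, 4 and 8. On content, "Stretching exercises and Tai Chi will be mainly included in the" courses.
- **Recall.** The leisure-time section of PASE in Appendix A asks: "In the past week, how did you participate in moderate sports such as table tennis, dancing, or tai chi".

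**The concern.** Participants know their arm: one arm is called weekly, trained and placed in peer groups. With a self-reported outcome, the remaining protection is an interviewer who has no stake in the answer and does not know the village's allocation. The plan does not secure this, and its scripts tell intervention participants that their coaches and their surveyors are one group. Someone who has been praised for reaching goals, and then reports activity to that group, has reason to answer generously. Nothing comparable happens in control villages. Because the outcome is a change, knowledge of allocation at the baseline interview would matter as well.

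The second mechanism is separate. If the week-8 session falls in the seven days that PASE covers, activity organised by the study is scored as the participant's leisure-time activity, in one arm only. The 8-week contrast could then rise without any change in what people do on their own, while the trial sets out to test sustainability too.

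**Working it through.** **1. Who interviews: the sections side by side**

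| Place | What it implies |
|---|---|
| Assessment Team; Data Management and monitoring | An assessment team interviews at all visits, including 8 weeks |
| Training Sessions | Sports experts teach |
| Appendix B, all four call scripts | The callers, as we, did both training and survey |
| Quantitative surveys; Telephone Counseling | Investigators administer questionnaires; investigators praise and assist |
| Community Level; Group Sharing | Sharing is led by investigators in one section, by the education team in the next |
| Quality Assurance, Personnel | Survey, interview and counselling staff are trained to common standards; the examples of divided work are logistics and site coordination |

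The first two rows describe separation and the third contradicts it. No row masks the interviewers or forbids them calls, training or group sharing.

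**2. Can the session enter the recall week?**

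Visits are timed from baseline and sessions by intervention week. The first-call script places both training and survey several days earlier, which suggests that baseline and the first session were close together. If they coincided, 8 weeks after baseline is day 56, and the preceding seven days are intervention week 8, which has a session. No visit window is given, nor the gap from baseline to week 1, nor the order of session and interview. Overlap is therefore likely but not documented.

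The frequency options are never, 1-2, 3-4 and 5-7 days. One added day changes the category of someone otherwise active on 0, 2 or 4 days (0 to 1, 2 to 3, 4 to 5). It leaves 1, 3, 5 and 6 days where they were. Session length, the item weights and the SD of the leisure-time score are not given, so this cannot be turned into an effect on the primary outcome.

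**3. The plan's sample size, reproduced**

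Inputs from Sample Size Computation: effect 0.42 SD, two-sided alpha 0.05, power 80%, design effect 2.1, 20% addition.

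- n = 2(1.960 + 0.842)² / 0.42² ≈ 89 per group; 90 with the t distribution. Stated: about 90.
- 90 × 2.1 = 189; 189 × 1.2 = 226.8, so 227; 2 × 227 = 454. All as stated.

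**4. What a reporting shift would do at that precision (illustration)**

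Effective n per arm = 189 / 2.1 = 90, so SE = √(2/90) = 0.149 SD. With no true effect and a differential shift b, the two-sided rejection rate is Φ(−1.96 + b/SE) + Φ(−1.96 − b/SE). The last column uses a noncentral t on 6 df (8 villages minus 2 arms). The values of b are assumed; the documents give none.

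| b (SD) | b / 0.42 | Normal test | t, 6 df |
|---|---|---|---|
| 0 | 0% | 5.0% | 5.0% |
| 0.05 | 12% | 6.3% | 5.9% |
| 0.10 | 24% | 10.3% | 8.8% |
| 0.15 | 36% | 17.2% | 13.7% |
| 0.20 | 48% | 26.9% | 20.6% |

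This shows how sensitive the test is. It does not estimate the bias.

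**The case against.** The other side has a good case. The staffing sections name separate teams and should outweigh a telephone greeting. The greeting's we may simply mean the study, and in the first call it refers to a survey around baseline, not to the 8-week interview. The script gives no order for survey and training, so a baseline interview held before any session fits it equally well. Tai Chi done in a session is real activity, and whether to count it is a question of estimand rather than misreporting. The 6-, 12- and 24-month visits are free of the overlap. A participant near the scripted example goal of Tai Chi twice a day is already in the top frequency category.

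Most of this stands, and it limits what can be claimed. A reader might infer that the same people coach and conduct the 8-week interview, that allocation was known at baseline, or that the week-8 session certainly lies in the recall week. The documents establish none of these.

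It does not remove the point. A team that is separate on paper can still know the arm, and no section says otherwise. The scripts are what staff read aloud, and they contradict the separation. The estimand question also has to be answered, because the overlap can occur at the primary time point.

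**Conclusion.** The plan leaves the masking of its only primary outcome undefined, contradicts itself on whether trainers and callers are separate from interviewers, and does not fix the order of session and interview at 4 and 8 weeks. The 8-week contrast is at risk of bias towards the intervention. A reader might go further and say that it is biased. The documents do not support that: the direction is plausible, but neither the existence nor the size of a bias can be derived from them.

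The illustrative rates rest on an assumed shift of 0.05 to 0.20 SD, the plan's design effect of 2.1 and 189 analysed participants per arm. They show only that a modest shift would matter at this precision. The recall overlap further assumes that intervention weeks run roughly parallel to weeks since baseline. This is a worthwhile and inexpensive correction, not a fatal flaw.

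**What to change.** 1. In Design, state that the blinded party is the outcome interviewers. Have PASE administered at all visits only by existing assessment-team members who take no part in training, calls or group sharing and are not told the village's arm. Reconcile Training Sessions, Data Management and monitoring, and Assessment Team with the four call scripts.
2. Complete the baseline interview before the first session and before allocation is disclosed to participants and interviewers.
3. Hold the 4- and 8-week PASE interviews before that week's study-run session. Figure 2 marks no session in weeks 3 or 7, so the recall week would then contain none. Do not instead tell interviewers to leave study-run sessions out of the count: participants would have to disclose them, which would unmask the interviewers.

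The cost is rostering, scheduling and edits to the text, with less flexibility over who interviews and when. The primary interview would precede the last of the three sessions. Masking by village will be imperfect, and participants' own tendency to give desirable answers remains.

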#### **b. Telephone counseling process (all intervention subjects)**

1. First of all, please ask: Hello, is this xxx?

---

2. Descript the intention of this call: We are the investigators performed physical activity training and questionnaire survey for you several days ago. Now we need to ask you some questions, can you please make it convenient for us now? (if it's not convenient now, ask the nearest available time)

3. Primary contents

1) Recent exercise situation: What types of exercise were you performing recently, how many times a day, and how many minutes each time for performing PA?

2) Set exercise goals: Your current exercise intensity is (great/okay/not enough), next week you can perform (moderate-intensity PA such as Tai Chi: 2 times a day and 20 minutes for each time or 40 minutes a day; vigorous-intensity PA such as running: 2 times a day and 15 minutes for each time or 20 minutes a day). We will call you every week to see if you have reached your goals.

3) Peer group: We assisted you to form a peer group to exercise together after the PA training, do you remember that? You are one of the members of group x (e.g., 1), and xx is the leader of your group. The exercise goal of your group is to xx (e.g., dance once a week and 20 minutes for each time). Please don't forget to exercise with your group.

**(2) Weekly Telephone Counseling Template After the First Time**

**a. Telephone counseling process (group leaders)**

1. First of all, please ask: Hello, is this xxx?

2. Descript the intention of this call: We are the investigators performed physical activity training and questionnaire survey for you. Now we need to ask about your exercise situation for the previous week, which is estimated to take 3 minutes, would that be convenient for you? (if it's not convenient now, ask the nearest available time)

3. Primary contents

1) Personal exercise goal: The exercise goal we set in counseling was xx (e.g., play Tai

---

Chi twice a day and 20 minutes for each time). Did you reach that goal last week? Do you think the current intensity and amounts of PA are appropriate?

2) Current difficulties: What were the reasons for your failure to reach the goal? Did you encounter any difficulties?

3) Peer group: You are the leader of your peer group, right? Did you organize your members to exercise together regularly? Have you reached the goal of xx (e.g., dancing once a week)?

a. If the goal was not achieved, ask why and record it.

b. If the goal was achieved, know about the positivity of group members, and if they were active, adjust the goal by increasing the amount and intensity of PA appropriately.

#### **b. Telephone counseling process (all intervention subjects)**

1. First of all, please ask: Hello, is this xxx?

2. Descript the intention of this call: We are the investigators performed physical activity training and questionnaire survey for you about x (e.g., 2) weeks ago. Now we need to ask about your exercise situation for the previous week, which is estimated to take 3 minutes, would that be convenient for you? (if it's not convenient now, ask the nearest available time)

3. Primary contents

1) Personal exercise goal: The exercise goal we set in the last counseling was xx (e.g., play Tai Chi twice a day and 20 minutes for each time). Did you reach that goal last week? Do you think the current intensity and amounts of PA are appropriate?

2) Current difficulties: What were the reasons for your failure to reach the goal? Did you encounter any difficulties?

3) Self-efficacy: Which aspects do you think you are doing well in your exercise, could you be more specific? (deliver encouragement). Are there any areas where you are not

---

doing well? What adjustments can be made in these areas?

4) Peer group: Have you participated in regular peer group activities (e.g., dance) during last week? Did the group leader (xxx) lead you to exercise regularly?

